### Secondary outcome measures

We will objectively measure performance change during treatment sessions using the Performance Quality Rating Scale (PQRS), a 10-point observation scale (1 = not able to do it all; 10 = being able to do the specified activity with good quality)
[18]. Videotapes of treatment sessions will be scored by trained occupational therapists blind to the study arm and session time point. The PQRS has been used in many of the previous studies on the CO-OP intervention
[32,33], with reported reliability of 0.72
[34]. We will further establish inter-rater reliability using videotapes from our pilot work. Intra-class correlation coefficients will be calculated and a coefficient of 0.7 will be considered sufficient
[32].

Three additional outcome measures will be used to determine the benefits of the experimental intervention on the perceived and observed impact of the executive dysfunction in everyday life and overall improved community integration. The Behavioural Rating Inventory of Executive Function – Adult is a standardized 75-item questionnaire that asks persons to rate the frequency with which particular aspects of the dysexecutive syndrome occur in their day-to-day lives, including emotional or personality changes, motivation changes, behavioural changes, and cognitive changes
[35]. This will be administered to both the participant and their significant other.

As improving performance on meaningful everyday life activities should ultimately have a positive influence on measures of community integration or community partici-pation, we will measure changes in community integration using the Mayo-Portland Adaptability Inventory Participation Index
[36], an 8-item questionnaire that includes items on financial management, work and school, social relationships and leisure. We will use both self and significant other versions.

The ability of participants to solve novel performance problems will be measured using two sub-scales of the Instrumental Activities of Daily Living Profile
[33], namely obtaining information and making a budget. In the first task, participants have to obtain specific information about how to get from one large urban area to another by a specified mode of transportation and in the second they have to prepare an annual budget within specific task constraints (e.g., income level, have to save for car). Both tasks will be videotaped and performance scored by a rater blinded to group and session on a three-point scale (independent, independent with difficulty, unable to complete task). Time to completion will also be recorded.

### Intervention

#### Experimental intervention

The adapted CO-OP intervention involves up to 15 hours of treatment delivered by a trained occupational therapist. Key elements of the approach are that: i. Participants are actively engaged in selecting their own treatment goals. ii. A meta-cognitive strategy is used (goal-plan-do-check) throughout each session to promote goal achievement. Participants are trained to use the meta-cognitive strategy as a way of planning and regulating their performance. Workbooks are provided to participants so that they, with the assistance of the clinician, can keep track of individual goals and plans. iii. During each intervention session, participants are ‘guided’ by the therapist to use the meta-cognitive strategy to identify their performance problem (i.e., dynamic performance analysis) and discover the plans or strategies that will solve these problems. ‘Guided discovery’ is a learning concept rooted in general principles of learning theory
[37]. There is evidence that the participant’s work of discovering the ‘solution’ or strategies is integral to the success of the intervention and contributes to the development of self-efficacy as participants can attribute their successes to their own plans
[38]. Guided discovery means that the therapist takes a non-directive approach; they can offer suggestions that point participants to feasible plans although these suggestions are not mandated. Participants decide which plans to ‘do’ , check to see which ones work and through the course of the intervention iteratively test a number of plans (plan-do-check) and learn that not all plans work; thus, they learn to self-monitor and correct their performance. iv. A focus in each session is on training participants to generalize and transfer their learning. This is done at each session by explicitly discussing with participants how else they have or could have used the identified strategies and how they will continue to use them. The combination of these features is unique and novel. To our knowledge, no other intervention utilizes all of these features and we believe this approach represents a major step forward in rehabilitation.

#### Control intervention – conventional occupational therapy

Participants in the control intervention will receive up to 15 hours of therapy from a trained occupational therapist provided with a similar ‘referral’ as to what might be received by a publically-funded community therapist in Ontario, Canada, namely age of participant, diagnosis, and reason for referral (in this instance the participant-identified difficulties in everyday life). The content of therapy will include one or more of the following: task-specific training in activities of daily living; environmental and task modifications; and provision and training in the use of compensatory memory devices
[39]. Although there are advantages and disadvantages to every control intervention, conventional therapy was chosen as it is highly acceptable to participants and therapists, maximizes equipoise, and has distinct benefits for knowledge exchange as the external validity (generalizability of the results) is maximized
[40,41].

### Planned analyses

Differences in participants’ baseline socio-demographic, injury related, and neuropsychological status will be characterized by using proportion for gender and mean and standard deviations for other variables. To address the primary objective regarding efficacy of the experimental treatment, the main analysis will be performed as follows. The mean and standard deviation of the primary outcome (self-rating of performance on untrained goals) will be reported for both study groups. An analysis of covariance model for performance rating at each of post-treatment and follow-up time points will be fit to examine the effect of intervention group. Baseline performance rating and treatment intensity (measured in hours) will be included in the model as linear, continuous covariates. The contrast between groups adjusted for baseline and treatment intensity will be reported along with 95% confidence interval. Secondary outcomes will be reported in a similar fashion.

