### Ethical considerations and informed consent

Ethics approval has been received from the Baycrest Research Ethics Board. A trained research assistant will explain the purpose of the study and potential risks to potential participants. Participants will receive an information letter about the study and there will be no time limit for them to consider implications, ask questions, and respond to the invitation to participate. Participants will be informed that they are free to withdraw from the treatment under study at any time for any reason although they will be invited to come back for post-training and follow-up assessments.

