### Randomization

Randomization will be done in blocks of four via a random numbers table. Following baseline testing and participant registration, the Research Assistant will open the next sealed opaque envelope.

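### The main ANCOVA adjusts for therapy hours received, a post-randomisation variable, so its contrast is not the as-randomised effect and is biased if hours differ by arm and relate to outcome

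*Protocol article*

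**What the plan says.** The Planned analyses section presents this model as the main efficacy analysis, not as a sensitivity analysis: "To address the primary objective regarding efficacy of the experimental treatment, the main analysis will be performed as follows". An ANCOVA is fitted at post-treatment and again at follow-up. Its covariates are given as: "Baseline performance rating and treatment intensity (measured in hours) will be included in the model as linear, continuous covariates". The result to be reported is: "The contrast between groups adjusted for baseline and treatment intensity will be reported along with 95% confidence interval". Means and SDs of the primary outcome are also given for each group, but no formal contrast without hours is specified. Secondary outcomes are to be handled in the same way.

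Three other sections fix what the hours variable can be:

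- **Dose in each arm.** For the experimental arm: "The adapted CO-OP intervention involves up to 15 hours of treatment delivered by a trained occupational therapist". For the control arm: "Participants in the control intervention will receive up to 15 hours of therapy".
- **Timing.** The Randomization section says: "Following baseline testing and participant registration, the Research Assistant will open the next sealed opaque envelope". Therapy follows that step.
- **Stopping therapy.** Under Ethical considerations and informed consent, participants are "free to withdraw from the treatment under study at any time for any reason although they will be invited to come back" for the later assessments.

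**The concern.** The Objective section asks whether CO-OP is more effective than conventional occupational therapy. That is a comparison of the treatments as assigned, and randomisation supports it directly. Hours received are not a baseline characteristic. They depend on attendance, engagement and withdrawal after allocation, and the two arms differ in content and therapist style, so assignment could plausibly affect them.

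Conditioning on such a variable can go wrong in two ways. If hours lie on the path from assignment to outcome, part of the treatment effect is removed. If hours and outcome share a cause such as engagement or severity, comparing participants at equal hours means comparing different kinds of people in the two arms, even when hours themselves do nothing. The contrast at stake is the one the plan names for the primary outcome, and the same model carries over to the secondary outcomes. Inviting people who stop therapy back for testing suits an as-randomised comparison, but the model then adjusts for the lower hours they received.

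**Working it through.** **1. The plan's own sample size.** Inputs from Sample size determination: d = 0.6, alpha 5% (taken as two-sided), power 80%. Normal formula: n = 2(1.96 + 0.84)²/0.6² = 43.6, so 44 per arm. The t-test version gives 44.6, so 45, as stated. Then 45/0.9 = 50 per arm. Power at 45 per arm is 80.4% (t-test) or 81.2% (normal). The calculation is sound. It assumes a plain two-group comparison with no hours term.

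**2. Which hours?** The ceiling is 15 h in both arms. Planned hours would be a constant and could not act as a covariate, so the variable must be hours received, which accrue after the envelope is opened.

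**3. Algebra.** Let θ be the within-arm slope of outcome on hours and δ the difference in mean hours (CO-OP minus control), both adjusted for baseline. For least squares:

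adjusted contrast = as-randomised effect − θ × δ

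The bias is zero if θ = 0 or δ = 0. The documents give neither.

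**4. Range on the SD scale.** Assume θ from 0.05 to 0.15 SD per hour, δ from −2 to +2 h, and a true d of 0.60.

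| θ | δ (h) | Adjusted d | Power, 45 per arm |
|---|---|---|---|
| 0.05 | +2 | 0.60 − 0.10 = 0.50 | 66% |
| 0.15 | +2 | 0.60 − 0.30 = 0.30 | 30% |
| 0.05 | −2 | 0.60 + 0.10 = 0.70 | 91% |
| 0.15 | −2 | 0.60 + 0.30 = 0.90 | 99% |

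**5. Range on the rating scale, hours having no effect of their own.** The pilot SDs give a pooled SD of √((1.33² + 0.98²)/2) = 1.17, taken as the total SD, so d = 0.6 is 0.6 × 1.17 = 0.70 points. Assume that an unmeasured engagement factor adds 1.5 h and 0.6 points per SD, and that hours have a further independent spread σ. Ignoring the cap, θ = (1.5 × 0.6)/(1.5² + σ²).

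| σ (h) | θ (points per h) | Adjusted, CO-OP +2 h | Adjusted, CO-OP −2 h |
|---|---|---|---|
| 0.5 | 0.9/2.5 = 0.36 | 0.70 − 0.72 = −0.02 | 1.42 |
| 1.5 | 0.9/4.5 = 0.20 | 0.70 − 0.40 = 0.30 | 1.10 |
| 3 | 0.9/11.25 = 0.08 | 0.70 − 0.16 = 0.54 | 0.86 |

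Simulation with the 15 h cap, 45 per arm and a control mean of 11 to 13 h agrees. The adjusted contrast is about 0.0 to 0.6 when CO-OP is set 2 h higher and about 0.85 to 1.4 when set 2 h lower. With no true effect, the false-positive rate runs from about 7% to 81%. Without hours in the model, the estimate is 0.70, power about 80% and the false-positive rate 5% throughout. These gaps are as set before the cap; the cap shrinks the realised gap when CO-OP is set higher.

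**6. Other mechanisms.** In large-sample runs with true d about 0.61, if hours rise with need rather than engagement, the directions reverse: adjusted d is 0.21 with CO-OP set 2 h lower and 0.99 with it set 2 h higher. If hours act purely as a mediator, at about 0.13 SD per hour, as-randomised effects of 0.50 and 0.99 both become about 0.76.

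**7. When it does no harm.** With equal mean hours, the adjusted and as-randomised estimates agree. With hours set 0.5 h apart and a weak shared factor (0.1 to 0.3 points per SD), the false-positive rate stays at 4 to 6%.

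**The case against.** The strongest defence is that the covariate is deliberate. The Background faults an earlier trial for not reporting whether time in therapy was controlled, so the aim is probably a comparison at equal therapy time. That aim is reasonable, but the common 15-hour ceiling already equalises planned time by design. Adjusting for hours actually received answers a different question and does not restore comparability between the arms.

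The common ceiling also limits how far the arms can drift apart, and nothing in the documents points to a gap of 2 h. This stands, and it is why the size cannot be stated as a finding.

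A reader might go further and infer that the reported result will be biased, or that type I error fails whenever mean hours differ. The documents do not support either. Bias needs a difference in mean hours and a non-zero relation of hours to outcome, and neither is given. A reader might also say that the plan yields no other efficacy information. It does report group means and SDs, from which a raw difference can be derived; what it lacks is a specified contrast without hours. Finally, the definition of the analysis population is commonly left to an SAP, which is not shown, so its absence is no part of this point.

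**Conclusion.** The point holds in conditional form. The main model includes a post-randomisation covariate, so the contrast named for reporting does not in general estimate the effect of assignment to CO-OP. It is biased upward or downward, with type I error unprotected, when mean hours differ by arm and hours relate to outcome. The form of the bias follows from least-squares algebra; its size in this trial is unknown.

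The ranges shown rest on assumed slopes, hour gaps, engagement effects and spread of hours, and on an SD from change scores in 6 + 6 pilot participants. No single figure within them should be quoted as the expected bias. The sample size is unaffected. The point still warrants correction because it concerns the main efficacy contrast, extends to the secondary outcomes, and costs almost nothing to remove.

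**What to change.** In Planned analyses, or in the SAP, define the primary contrast at each time point as the ANCOVA on randomised group and baseline rating only, with participants compared in their assigned arm. Apply the same rule to the secondary outcomes, using each outcome's own baseline. Report hours received by arm descriptively. Any hours-adjusted or dose analysis, including a mediation or complier-type analysis, can stay if it is labelled supplementary or exploratory and its assumptions are stated.

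The cost is a change of a sentence or two, made before unblinding; the Trial status section records 42 of the planned 100 enrolled at submission. No new data or participants are needed, and 45 per arm still gives about 80% power.

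The downside is some loss of precision if hours turn out balanced and prognostic. In one run with equal mean hours and the strong engagement link assumed above, power was 87% with hours in the model and 79% without. In the other direction, if hours correlate with group at 0.3 or 0.5, collinearity alone cuts power from 81% to 77% or 69%.

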## Discussion

This paper describes the protocol for testing the efficacy of an ecologically valid approach to managing executive dysfunction. We hypothesize that participants trained in the adapted CO-OP approach and their significant others will report and demonstrate significantly more improvement on self-identified difficulties in everyday life than participants receiving conventional therapy. We also hypothesize that the strategies learned by participants receiving the CO-OP training will be applied in other areas of everyday life, will be reported by participants and their significant others and observed on measures of the impact of executive dysfunction in everyday life and on overall community integration.

Comparing the CO-OP approach to conventional occupational therapy will ultimately allow us to make recommendations about the treatment of people with stroke and acquired brain injury.

## Trial status

This article was submitted on July 4, 2013. To date, 42 participants have been enrolled.

## Abbreviations

CO-OP: Cognitive orientation to daily occupational performance; COPM: Canadian occupational performance measure; PQRS: Performance quality rating scale.
